### Data analysis

Descriptive statistics and exploratory plots (boxplots or histograms) will be used to describe the outcome variables (e.g., health state, preference based measure of health, hospital utilisation, and costs) and potential predictors (e.g., age, employment status).

SF-36 scale raw scores will be transformed to a 0 to 100 scale. Results will be analysed using the 8 scales and the summary scores where appropriate. Scatterplots of the relationship between variables will be examined to check for linearity or potentially non-linear associations. Mean SF-36 scores will be plotted over time by demographic and disease subgroups to visually examine chronic disease progression. Regression models will be used to examine the effect of time and predictors on post-intake SF-36 scores. The scores will be modelled at 3- to 12-months with the baseline score as a predictor in order to: i) analyse the change from baseline; ii) help control for regression to the mean [36]. Mixed models will be used with subject-specific intercepts to model the dependence in results over time from the same subject. The lasso technique will be used to choose the best set of predictor variables from an initially large set of potentially important variables [37]. The residual distribution of the best model will be examined to check that it is approximately normally distributed with no large outliers. The count outcome variables (i.e., cost, days in hospital, and number of hospitalisations) will be analysed using the model described above but assuming a Poisson distribution.

The predictors to be examined in all of the models will be: BMI and waist measurement, disease burden, number and type of comorbidities, self-reported health perception, age, gender, indigenous status, country of birth, language (other than English), marital status, home ownership, highest level of education, occupation and employment status, length and type of intervention; and baseline psychological distress or wellbeing, functional and structural social support, and physical function. Health (measured using the SF-36) and the preference based measure of health will be examined as predictors for count outcomes.

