Adjustment will made for wave missing data (where a subject misses an entire visit) using inverse probability weighting [38]. This is a two-stage procedure. In the first stage a logistic regression model is used to predict which subjects are more likely to be missing at each follow-up time. This model will include time, demographic factors and comorbidity factors collected at baseline. The probability of each subject being missing at each time is then calculated and inverted to create a weight that can be used in the regression models described above. As an example, if men at 12-months have a 0.5 probability of responding, then the weight for men is 2 so that the results for those men who responded at 12-months are doubled. This will enable a sensitivity analysis with comparison to the complete case analysis to be conducted.

The health of the study sample (using SF-36 scores) will be compared to Australian normative data [39] matched on select sociodemographic variables such as age, gender and select chronic diseases using unpaired t-tests with 95% confidence intervals.

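### Visit-level inverse-probability weights lose force in a random-intercept model: a weight of 2 counts for less than double, so the attrition check under-corrects

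*Protocol article*

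**What the plan says.** All the relevant text is in the Data analysis section of the Protocol article.

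- **Outcome model.** Follow-up SF-36 scores are modelled with the baseline score as a predictor, and the lasso selects the other predictors. For repeated scores: "Mixed models will be used with subject-specific intercepts to model the dependence in results over time from the same subject".
- **Weights.** A logistic model predicts missingness at each follow-up. Its content: "This model will include time, demographic factors and comorbidity factors collected at baseline". The probability for each subject at each time is inverted to "create a weight that can be used in the regression models described above".
- **Stated effect.** The worked example gives male clients whose response probability is 0.5 a weight of 2. The claimed result: "so that the results for those men who responded at 12-months are doubled".
- **Purpose.** "This will enable a sensitivity analysis with comparison to the complete case analysis to be conducted".

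The general rule inverts the probability of being missing, whereas the example inverts the probability of responding. That mismatch is a separate matter. The example's reading is used here, and the two coincide at 0.5.

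**The concern.** The weights are specific to a visit, and the models they enter contain a client-level intercept. A visit-level weight makes that visit's residual count as more precise but leaves the between-client variance as it was. A client's pull on the estimated mean therefore grows by less than the weight, and the property claimed in the example does not hold for the model named.

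The weighted analysis exists to show whether attrition matters, by comparison with the complete-case analysis. A diluted correction pushes that comparison towards agreement. This can mislead when something that drives drop-out also affects the score but is absent from the outcome model. The plan allows this, because the lasso chooses the outcome predictors while the missingness model is specified separately.

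**Working it through.** **1. The plan's own figure.** Weight = 1/P(respond) = 1/0.5 = 2. It reproduces.

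**2. What a weight of 2 does in the named model.** Let τ² be the between-client variance, σ² the within-client variance, and ICC = τ²/(τ² + σ²). With visit-level weights the covariance for a client is V = τ²J + σ²·diag(1/w). For k visits of equal weight w, the client's influence on the mean is 1/(τ² + σ²/(kw)). Going from w = 1 to w = 2 multiplies it by

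M = [ICC + (1 − ICC)/k] / [ICC + (1 − ICC)/(2k)].

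| Residual ICC | One visit | Three visits, all weighted 2 |
|---|---|---|
| 0 | 2.00 | 2.00 |
| 0.25 | 1/0.625 = 1.60 | 0.500/0.375 = 1.33 |
| 0.5 | 1/0.75 = 1.33 | 0.667/0.583 = 1.14 |

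The article gives no ICC, so the range is an assumption. With the baseline score as a covariate and an equal correlation ρ between all visits, the residual ICC is ρ/(1 + ρ), which cannot exceed 0.5. Full doubling needs an ICC of 0, where the random intercept does nothing.

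**3. Effect on a mean, by hand.** Assume half the clients are men, men respond with probability 0.5 and women always, drop-outs miss every follow-up, true means are 0 and 10 (overall 5.0), and neither sex nor baseline score is in the model.

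- Unweighted: 10 × 0.5/(0.5 + 0.25) = 6.67, a bias of 1.67.
- Weighted: 10 × 0.5/(0.5 + 0.25M). M = 2 gives 5.00. The three-visit M gives 6.00 at ICC 0.25 and 6.36 at ICC 0.5.
- Bias removed: 0.67/1.67 = 40% and 0.30/1.67 = 18% (unrounded).

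**4. With the baseline score as a covariate, as planned.** Under the same assumed inputs (half men, response 0.5, a 10-point difference, factor not in the outcome model), simulation gives about 25-32% of the bias removed when clients miss all visits, and about 70-80% when only 12 months is missed.

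**5. A second set of assumed inputs.** SD 20, 12-month response 50% versus 90%, an 8-point effect at 12 months, residual ICC about 0.23 to 0.52, and an unweighted mixed-model bias of about 1.0 to 1.2 points.

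| Setting | Bias left after visit-level weights | Removed |
|---|---|---|
| All-or-none follow-up, constant effect | 0.6 to 0.9 | 22-46% |
| All-or-none follow-up with a growing effect; rising or intermittent attrition; 12 months only | 0.2 to 0.5 | 56-79% |

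Weighted estimation under independence left bias within about 0.1 point throughout. With the factor and its time interaction in the outcome model, weighted and unweighted mixed models were both essentially unbiased.

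**The case against.** **A client-level weight would double.** A probability weight that multiplies a client's whole likelihood contribution does double that client's influence inside a random-intercept model, at given variance components. In a run of the complete drop-out case (ICC 0.5, truth 5.0), the unweighted estimate was about 6.6, visit-level weights gave about 6.3 and client-level weights about 4.9. This stands, so it would be wrong to say that every kind of weight is diluted. But the article computes a probability for each subject at each time, puts time in the missingness model and gives an example tied to 12 months. One weight per client would be a different procedure.

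**A condensed article may leave the implementation to the full plan.** This is fair as to software detail. The article does, however, name the model, describe time-specific weights and state what they achieve. Following that text under-corrects, which is more than a missing detail.

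**The harm needs a chain of events.** Gender, other demographics and comorbidities are all candidate predictors, and a factor with a 10-point effect, twice the upper end of the 3 to 5 points cited as clinically important, is a poor candidate for being dropped. The baseline score also removes part of a stable difference: in one run the unweighted bias fell from about 1.6 to 0.9 points. Both points stand and limit how often and how much this matters. They do not make the weight work as described.

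**A stronger reading is tempting**: that the random intercept absorbs the weights, so the check is bound to agree falsely. The article does not support this. Its own example concerns the 12-month visit, and when only that visit is missed most of the correction survives. Agreement is also correct whenever the outcome model already holds the predictors of drop-out.

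**Conclusion.** The point holds as one of attenuation. For visit-level weights in the stated random-intercept models, the doubling claim is inexact: the effective multiplier is about 1.6 to 1.3 (one visit) or 1.3 to 1.1 (three equally weighted visits) at residual ICC 0.25 to 0.5. The share of bias removed depends on the missingness pattern. It is about 25-32% for loss of all follow-up with a constant difference and about 70-80% for loss of the 12-month visit only, under the assumed inputs. The multipliers follow from algebra once an ICC is assumed; the bias figures rest on assumed response rates, effect sizes and correlations, none of which the article supplies. False reassurance is possible, not certain, and requires a predictor of drop-out, or its time interaction, to be missing from the outcome model. Only a sensitivity analysis is affected, but the error works against its purpose and is cheap to correct.

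**What to change.** Reword the sentence that sends the weights into the mixed models. Run the weighted sensitivity analysis as weighted estimating equations with an independence working correlation and client-clustered robust standard errors, so that a weight of 2 does count double. Compare it with the same equations unweighted, so that the contrast reflects the weights alone and not a change of estimator. Keep the unweighted mixed model alongside.

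The cost is a sentence of analysis text, a different procedure call and somewhat wider intervals in the weighted analysis. If the authors prefer to stay with a mixed model, the text should say that the weights enter once per client and explain how that fits missingness that varies by visit.

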### Study objectives

#### ***Aims***

1. To examine the effectiveness of the service up to 12-months post-intake in improving a range of health outcomes (including length of stay in hospital, number of admissions, health state, preference based health state, and health-related costs).

2. To examine the effect of a range of factors including comorbidities, sociodemographic factors, and type of intervention received, on the health state, preference-based health state, length of stay in hospital, number of admissions, and health-related costs of people attending the service up to 12-months post intake.

3. To determine the difference in health between clients attending the service before and after receiving intervention and the general population using Australian population normative data.

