#### ***Hypotheses***

1. Health will be maintained or improve over time from intake (baseline) to 12-months after intake with a small average effect size anticipated for improvement (effect size ≤ 0.2).

2. Health outcomes will be moderately to strongly and negatively associated with the number of chronic diseases (effect size ≥ 0.5).

3. Days in hospital and inpatient admission costs will decrease after intake to the service compared with before intake to the service.

4. The health of clients attending the service will be worse than the general population using Australian population normative data at all times (effect size ≥ 0.2).

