### Sample size and power

A minimum sample size of 130 participants is required to examine the change over time from baseline to 12-months post-intake of the SF-36; using a one-group longitudinal design, a power of 80% with a two-sided type 1 error of 5% to detect a difference of at least 5 points in the social functioning scale of the SF-36 using a t-test [33]. Three to five points of change in SF-36 scores has been reported as the minimally clinically important difference [33,34] and is equivalent to a small effect size for those with chronic diseases [34]. A small effect size is anticipated for changes in health over 12-months based on the small to large effect sizes found in treatment effectiveness studies using the SF-36 in related chronic disease studies over similar times [7,12,34,35] and the high percentage of clients with multiple chronic diseases attending the service prior to the study commencement, for whom moderate to large effect sizes are unlikely. The sample size calculation was based on the social functioning scale of the SF-36 as this outcome would likely show the smallest difference and therefore need the largest sample size. Therefore, provided the study sample size exceeds 130 participants, this investigation should have greater than 80% power for all outcomes.

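### The normative comparison matches on age, gender and disease but uses unpaired t-tests, so its intervals are somewhat too wide and some power is lost

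*Protocol article*

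**What the plan says.** Aim 3 is "To determine the difference in health between clients attending the service before and after receiving intervention and the general population using Australian population normative data". Hypothesis 4 expects clients to be "worse than the general population using Australian population normative data at all times (effect size ≥ 0.2". The only test named for this comparison is in the last paragraph of Data analysis, where the study sample's SF-36 scores are set against published norms "matched on select sociodemographic variables such as age, gender and select chronic diseases using unpaired t-tests with 95% confidence intervals".

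The article does not say whether the norms are individual records or tables by stratum. It does not say whether matching is one-to-one, by frequency or by stratum, and it gives no size for the norm sample.

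The sample size section concerns a different question: "A minimum sample size of 130 participants is required to examine the change over time from baseline to 12-months post-intake of the SF-36". It contains no calculation for Hypothesis 4, only a general statement that power will be above 80% across outcomes once 130 is exceeded.

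**The concern.** One sentence sets up a matched comparison and then names a test for two unmatched samples. Once the groups have the same mix of age, gender and disease, the part of SF-36 that depends on those variables cancels from the difference in means. The unpaired t-test still counts that part as noise. Its standard error is then too large whether matching is by pairs or by equal stratum counts.

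The article itself expects such dependence. Hypothesis 2 predicts a moderate to strong association between health and number of chronic diseases. The section on disease burden reports that comorbidity scores correlate with the SF-36. Data analysis lists age, gender and type of comorbidity as predictors. None of this gives a value for the variance explained, and matching on selected diseases is not the same as matching on disease count.

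At stake is precision. The Discussion uses this comparison to judge how severe the cohort's health problems are, so interval width matters, and Hypothesis 4 starts at a small effect.

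**Working it through.** **The plan's own figure.** The 130 is for 80% power, two-sided 5%, "to detect a difference of at least 5 points in the social functioning scale of the SF-36 using a t-test" in one group. No SD is stated, so it can only be solved backwards: n = (SD × 2.802 / 5)², with 2.802 = 1.960 + 0.842, gives SD = 5 × √130 / 2.802 = 20.35, an effect size of 5 / 20.35 = 0.246. This is attainable, but it concerns within-person change, not the normative comparison.

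**Inputs for the check.**
- Effect size 0.2: the lower bound in Hypothesis 4.
- 130 clients: the stated minimum, borrowed here.
- 130 norm subjects: assumed.
- R², the share of SF-36 variance explained by the matching variables (for one-to-one pairs, the within-pair correlation): not stated; range 0.1 to 0.3 assumed.
- SD = 1 in both groups.

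**Formulas.**
- Standard error used by the unpaired test: √(2/130) = 0.124.
- True standard error after matching: √(2(1 − R²)/130).
- Interval width ratio: 1/√(1 − R²).
- True type I error of the unpaired test: 2Φ(−1.96/√(1 − R²)).
- Power, unpaired: 1 − Φ((1.96 × 0.124 − 0.2)/true SE).
- Power, matching kept: 1 − Φ(1.96 − 0.2/true SE).

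| R² | True SE | Width ratio | Type I error, unpaired | Power, unpaired | Power, matching kept |
|---|---|---|---|---|---|
| 0 | 0.124 | 1.00 | 5.0% | 36% | 36% |
| 0.1 | 0.118 | 1.05 | 3.9% | 36% | 40% |
| 0.2 | 0.111 | 1.12 | 2.8% | 35% | 44% |
| 0.3 | 0.104 | 1.20 | 1.9% | 34% | 49% |

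**Simulation with the actual t-tests.** One-to-one pairs gave power of 35% against 39%, 34% against 43%, and 33% against 48% at 0.1, 0.2 and 0.3, about a point below the normal approximation.

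**Does it need real pairs?** No. Norms drawn to the clients' stratum counts, with no pairing, gave unpaired type I error of 3.9%, 3.0% and 1.8%, and power of 35% against 39%, 35% against 43%, and 34% against 48%.

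**Very large norm sample.** With the norm's sampling error negligible, the true standard error is √(1 − R²)/√130. Power using the full SD is 63%, 64% and 65% at R² of 0.1, 0.2 and 0.3, against 67%, 72% and 78% using the residual SD. The width ratios are unchanged.

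**The case against.** The strongest case against is that the norms are external and the article describes no pairs. If clients in each age, gender or disease stratum were compared with the norm for that stratum, one test per stratum, the matching variables would be constant within each test and an unpaired t-test would be right. That reading is possible, and the mechanics may be set out in a fuller document. But the sentence compares the study sample as a whole, and for that comparison the named test does not fit the matching.

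Several stronger readings are tempting, and the article does not support them:

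- **That the power for Hypothesis 4 is wrong.** No such power is stated. The general claim of more than 80% does fail at an effect size of 0.2 with about 130 clients (36% against an equal norm group, about 63% against a very large one). The cause is sizing for a within-person change, and keeping the matching does not reach 80% in the range shown.
- **That the test could produce a false finding.** The error runs the other way: type I error falls below 5%.
- **That power is roughly halved.** This needs R² near 0.5 (31% against 62%), for which the article gives no basis.
- **That the loss builds up over the four visits.** Hypothesis 4 does refer to all times, but no figure for this can be derived.

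Hypothesis 4 also allows effects above 0.2. At an assumed deficit of 0.5, unpaired power with 130 per group is already about 98%, so the choice of test would show mainly in interval width.

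A final objection concerns the obvious repair. Subtracting a stratum mean and running a one-sample t-test treats the norm as error-free. With 130 clients, N norm subjects in proportionate strata and equal residual variance, type I error becomes 2Φ(−1.96/√(1 + 130/N)): 8.1% for N = 500 and 6.5% for N = 1,000. This stands, and it shapes the fix.

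**Conclusion.** The point holds in a modest form. Read as one comparison of the whole sample, the plan matches and then ignores the matching. If the matching variables explain 10% to 30% of SF-36 variance, intervals are about 5% to 20% too wide. At an effect size of 0.2 with 130 per group, some 4 to 15 percentage points of power are given up (35% against 39%, to 33% against 48%).

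These sizes rest on the assumed R², the assumed norm sample and the borrowed 130. The loss shrinks towards nothing if matching explains little, and matters less for detection if the true deficit is large. The conclusion is lost precision, not an invalid test.

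**What to change.** In Data analysis, state whether the norms are individual records or stratum tables and how they are matched, and replace the unpaired t-tests with the analysis that follows:

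- **Individual records, paired to clients:** mean within-pair difference with a paired t-test and 95% interval.
- **Individual records, frequency-matched:** regression of SF-36 score on group, adjusted for the matching variables.
- **Stratum tables only:** a directly standardised difference, D = Σ wₛ(client meanₛ − norm meanₛ), where wₛ is the share of clients in stratum s. Its variance is Σ wₛ²(client varianceₛ/client nₛ + norm varianceₛ/norm nₛ), so that the norm means are not treated as known without error.

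Apply the same method at each visit. The cost is a few lines of text and slightly more analysis work, with no new client data. The stratum version needs SDs and counts for the norms as well as means. If the matching variables explain little, the result will be almost the same as now.

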## Background

A unique student-led interdisciplinary chronic disease health service was established in regional Australia in 2010 to address workforce shortages and spiralling rates of chronic disease in rural and regional Queensland. The service also aimed to improve local clinical placement options for allied health students. The service was established in a shopping centre with easy access using public transport.

Demographics of the people attending the service in the first year of the service (prior to commencement of the study) revealed very high rates of multimorbidity (97%) and higher rates of indigenous clients (7.1%) compared with the local community (5.9%) [1]. These demographics are relevant to the expected health outcomes of people attending the service as people with multimorbidity have worse health outcomes [2], and place a larger burden on the healthcare system than those with a single chronic disease. Additionally, indigenous Australians generally have worse health outcomes than non-indigenous Australians; including mortality and disability rates [3].

Interdisciplinary care has been promoted as a solution to maintain or improve the quality of healthcare, particularly in regional and rural areas [4-6] where health service disparity, healthcare access, and a worse burden of chronic diseases may place people living in these areas at a disadvantage in comparison to metropolitan areas [7]. Despite this, there are few high quality studies that evaluate the effectiveness of interdisciplinary care for chronic disease or primary care [8], even in metropolitan areas.

This paper describes the study protocol of a longitudinal evaluation of a unique interdisciplinary health service established in a regional Australian city to address chronic disease. The study will estimate the health outcomes and associated health costs of people attending the service.

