### Participants and selection criteria

All clients who attended the service will be eligible to participate. The following are inclusion criteria: presence of at least one chronic disease; aged 18 or older; and attendance at their first intake appointment. In addition, clients will be required to attend a minimum of one intervention session at the service for follow-up data to be included in analyses of clinic effectiveness over time. The following are exclusion criteria: a severe communication disability or behavioural disorder that would compromise the ability to participate in the intervention program or complete the questionnaires; a cognitive deficit that impairs the ability to read and write; and known pregnancy or up to 6-months postpartum that would influence body mass index (BMI), waist measurements, and possibly other outcomes. All participants receive individually tailored care prescribed by the service.

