## Discussion

This study is a broad evaluation of the client health outcomes and healthcare costs of people attending a unique regional service that is attempting to meet the health needs of regional and rural Australians with chronic disease. The study will provide preliminary evidence on the effectiveness of interdisciplinary intervention for this clinical population; an area that has received little investigation to date [8]. In addition, it will provide evidence regarding the influence of a range of variables including multimorbidity on the health and health costs of people with chronic disease in a rural and regional area. Comparison of the health state of people attending the service to the general population will determine the severity of health issues in the study population. The combined evidence will greatly assist in informing future service delivery and research.

The need for rigorous non-randomised studies in community settings has been highlighted by Bettger and Stineman [40] as these studies can identify target populations and appropriate outcomes for measurement that are important foundations for randomised controlled trials (or can even inform if randomised trials are required at all). Of relevance to the many participants with multimorbidity who are likely to be recruited in this study, randomised controlled trials to evaluate long-term outcomes have been discussed as inappropriate for people with conditions likely to worsen over time regardless of the intervention received [40]. Thus this longitudinal study will provide important information on the progressive impact of chronic disease in people in regional and rural areas who are involved in this unique intervention program. Specifically, the study will contribute knowledge about hospital use, health and healthcare costs associated with chronic disease for people in regional and rural areas over time. The factors that influence these changes will also be investigated.

Economic and health-related outcomes from this investigation will inform other health services throughout Australia (and elsewhere) who are considering adopting comparable models of service delivery. Outcomes from this study will also inform future research investigating health service needs and clinical needs for comparable populations.

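### Matching the norms on chronic disease changes the general-population comparison in Hypothesis 4 and may understate the difference

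*Protocol article*

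**What the plan says.** Three places in the protocol article name the general population as the comparator.

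- The third item under **Aims** reads "To determine the difference in health between clients attending the service before and after receiving intervention and the general population using Australian population normative data".
- The fourth item under **Hypotheses** reads "The health of clients attending the service will be worse than the general population using Australian population normative data at all times", with "effect size ≥ 0.2".
- **Discussion**: comparing the health of attendees "to the general population will determine the severity of health issues in the study population".

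One place says how this will be done. **Data analysis** compares SF-36 scores with Australian normative data "matched on select sociodemographic variables such as age, gender and select chronic diseases using unpaired t-tests with 95% confidence intervals". No comparison without disease matching is described.

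Two further statements matter. **Participants and selection criteria** requires "presence of at least one chronic disease". **Hypotheses**, item 2, reads "Health outcomes will be moderately to strongly and negatively associated with the number of chronic diseases (effect size ≥ 0.5" (the closing bracket follows). The **Background** adds that 97% of those attending in the service's first year, before the study began, were multimorbid.

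**The concern.** Age and gender are background characteristics. Standardising the norms on them leaves the question intact: are clients worse off than people of the same age and gender in the general population? Chronic disease is different, because it is the condition for entering the cohort and, on the plan's own expectation, a correlate of poor health. Once the norms are restricted to people with the same selected diseases, the comparator is no longer the general population. The sentence in Data analysis groups chronic diseases with the sociodemographic variables, so the change of question is easy to overlook.

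What is at stake is the answer to Aim 3. Clients could be clearly worse off than the general population while the matched contrast shows a small difference, or one below 0.2. The severity of their health problems would then be reported as less than it is.

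**Working it through.** **Step 1: which question each passage asks.**

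| Place | Comparator |
|---|---|
| Aims, item 3 | General population |
| Hypotheses, item 4 | General population, at all times |
| Discussion | General population, as a gauge of severity |
| Data analysis | Norms matched on age, gender and selected chronic diseases |

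The first three agree. The fourth is the only operational statement, and it differs from them.

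**Step 2: direction of the effect.** All clients have at least one chronic disease; the general population includes people with none. Hypothesis 2 expects a negative association between number of diseases and health. If the selected diseases go with worse health, removing people without them from the comparator lowers its mean SF-36 score and pulls the difference toward zero.

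**Step 3: size.** The plan gives no figure for this comparison: no normative means, no disease-specific scores and no sample size. Its 130 participants are for change over time in social functioning. There is therefore no stated figure to reproduce, and what follows is an illustration on assumed inputs.

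- G: true standardised gap between clients and the age- and gender-matched general population (assumed 0.3 to 1.0).
- f: share of that gap carried by the matched diseases (assumed 0 to 100%).
- The same SD is used to standardise both contrasts.

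Residual gap after disease matching = G × (1 − f).

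| G | f = 25% | f = 50% | f = 60% | f = 75% | f = 100% |
|---|---|---|---|---|---|
| 0.3 | 0.225 | 0.15 | 0.12 | 0.075 | 0 |
| 0.5 | 0.375 | 0.25 | 0.20 | 0.125 | 0 |
| 0.8 | 0.60 | 0.40 | 0.32 | 0.20 | 0 |
| 1.0 | 0.75 | 0.50 | 0.40 | 0.25 | 0 |

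The residual drops below the 0.2 of Hypothesis 4 when f exceeds 1 − 0.2/G:

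- G = 0.3: 1 − 0.2/0.3 = 33%
- G = 0.5: 1 − 0.2/0.5 = 60%
- G = 0.8: 1 − 0.2/0.8 = 75%
- G = 1.0: 1 − 0.2/1.0 = 80%

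Without disease matching the contrast stays at G.

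**The case against.** **The wording is loose.** The matching variables are introduced as examples, and the sentence does not say that all are applied at once. It could mean separate comparisons with strata by age, by gender and by condition. That is a fair reading, and the normative source is not at hand to settle it. Even so, chronic disease is named as a matching variable for the only analysis of Hypothesis 4, and nowhere does the text describe a comparison free of it. Which diseases are selected may properly be left to the full protocol or analysis plan, and is not counted as a fault here.

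**The bias is conservative.** A deficit found against people with the same diseases would support Hypothesis 4 all the more. This stands: the risk runs one way, toward an understated or missed difference. It also touches only one aim of a study described as preliminary; Hypotheses 1 to 3 are unaffected.

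**Stronger readings a reader might infer.** Three are not supported.

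- *That matching removes the gap altogether.* Only selected diseases are matched. Differences in unmatched diseases, number of conditions, severity and referral to a clinic remain.
- *That the loss is 0.5 SD or more, taken from Hypothesis 2.* That figure concerns the association between health and number of diseases. It is not a client-versus-population difference, and the text does not express it in SD units. Setting it against 0.2 also compares two lower bounds.
- *That low power demonstrates the problem.* With 130 clients and norms treated as fixed, power at a difference of 0.2 is Φ(0.2 × √130 − 1.96) = Φ(0.32) ≈ 63%. This applies to any true difference of 0.2, matched or not, and only at exactly 130 clients, which the plan calls a minimum. It says nothing about disease matching.

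**Conclusion.** The mismatch stands on the text. The aim, the hypothesis and the Discussion name the general population, while the analysis as written compares clients with people who share selected chronic diseases. The part of the gap carried by those diseases is taken out, so the Hypothesis 4 difference may be understated.

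Confidence is high for the mismatch, and good for its direction provided the matched diseases go with worse health, as the plan's own Hypothesis 2 suggests. The size is unknown. The 60% break-even for a gap of 0.5 SD, and the range of 33% to 80% for gaps of 0.3 to 1.0 SD, rest on assumed gaps and a common SD, not on figures in the document. No number stated in the plan is wrong on this point. It should be corrected because a stated hypothesis depends on it and the correction is cheap.

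**What to change.** Amend the last paragraph of Data analysis to separate two comparisons.

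1. **For Aim 3 and Hypothesis 4:** match or standardise the normative data on age and gender, with other sociodemographic variables optional, and not on chronic disease. Report the standardised difference with its 95% confidence interval at baseline and at 3, 6 and 12 months, and judge each against 0.2.
2. **As a separate question:** keep the disease-matched comparison, labelled as clients versus people with the same conditions, with the matching diseases named before the data are examined. Do not use it to decide Hypothesis 4 or to describe severity relative to the general population.

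The cost is a change of wording and one additional comparison using the same normative source. No further data from clients are needed, and the plan already intends to use age and gender for matching.
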